### Interim analyses {21b}

Pre-specified interim analyses will be used to guide the adaptive design while controlling type 1 error inflation and power.

### Methods for additional analyses (e.g., subgroup analyses) {20b}

Exploratory pre-specified subgroup analysis will be performed. The primary endpoint will be repeated stratified by each subgroup. The primary endpoint and the prongs of the CCS will be reported. The stratifications will be done within treatment arm and an exact *p* value with associated 95% confidence interval will be reported. Additional analyses will be done as appropriate for additional clinical context.Age (split at median)SexNumber of vertebral level(s) treated (1 vs. 2)Baseline Pfirrmann gradeBaseline Modic changes

### Methods in analysis to handle protocol non-adherence and any statistical methods to handle missing data {20c}

Participants lost to follow-up may produce bias in this study. Reasons for discontinuation will be evaluated and characterized. Participants without month 12 data will be included through statistical imputation. The participants will be included in the analysis using Bayesian multiple imputation which may include covariates to aid in the imputation, including age, sex, body mass index, and race/ethnicity.

A sensitivity analysis will be conducted and is an important tool for additional characterization of missing data. A tipping point analysis will be provided to characterize the robustness of the primary study results. The tipping point analysis assigns every combination of success and failure to each participant missing the CCS. The tipping point makes no assumptions on the reason for missingness.

### Plans to give access to the full protocol, participant-level data, and statistical code {31c}

In the event of a study-specific publication, the subject-level datasets and derived variables used and/or analyzed during the trial will be made available, subject to any existing ethical or legal constraints, by the corresponding author upon reasonable request. The data sharing plan will adhere to the standard clinical trial reporting guidelines.

## Oversight and monitoring

### Composition of the coordinating center and trial steering committee {5d}

The clinical site of the principal investigator is the Spine and Nerve Centers of the Virginias (Charleston, WV, USA). This trial does not have a steering committee.

### Composition of the data monitoring committee, its role and reporting structure {21a}

This trial employs two independent medical monitors to adjudicate all adverse events and deviations from protocol.

### Adverse event reporting and harms {22}

An AE is any untoward medical occurrence in a participant or clinical investigation participant administered a pharmaceutical product and which does not necessarily have to have a causal relationship with this treatment. An AE can therefore be any unfavorable and unintended sign (including an abnormal laboratory finding, for example), symptom, or disease temporally associated with the use of a medicinal product, whether or not considered related to the medicinal product.

It is the responsibility of investigators, based on their knowledge and experience, to determine those circumstances or which should be considered adverse events.

A serious AE (SAE) is any untoward medical occurrence that:Results in death,Is life-threatening,Requires inpatient hospitalization or prolongation of existing hospitalization,Results in persistent or significant disability/incapacity,Is a congenital anomaly/birth defect, orIs an important medical event.

Note: The term “life-threatening” in the definition of “serious” refers to an event in which the participant was at risk of death at the time of the event; it does not refer to an event which hypothetically might have caused death if it were more severe.

Medical and scientific judgment will be exercised in deciding whether expedited reporting is appropriate in other situations, such as important medical events that may not be immediately life-threatening or result in death or hospitalization but may jeopardize the participant or may require intervention to prevent one of the other outcomes listed in the definition above. Examples include allergic bronchospasm, convulsions, and blood dyscrasias or development of drug dependency or drug abuse.

Note:A procedure is not an AE or SAE, but the reason for the procedure may be an AE or SAE.Pre-planned (prior to signing the ICF) procedures or treatment requiring hospitalizations for pre-existing conditions that do not worsen in severity are not SAEs.

Unexpected AE (UAE) or suspected adverse reaction refers to an event or reaction that is not listed in the investigator’s brochure or is not listed at the specificity or severity that has been observed; or, if an investigator’s brochure is not required or available, is not consistent with the risk information described in the general investigational plan or elsewhere.

Possible adverse events may include:Bladder or bowel dysfunctionCerebrospinal fluid fistulaDisorder of potency or disorder of sexual sensibilityEpidural bleedingsHematomaImmunologic response (the possibility that a patient may develop alloantibodies should be considered for any patient who might be a future recipient of allograft tissue or cells)Infections (from local infections such as superficial wound infections up to spondylodiscitis and/or meningitis)Neurological deterioration as serious as lesions of the cauda equina such as transient radiculopathy, cauda equina syndrome, or paraplegia secondary to ascending bleeding or infectionPain and/or inflammationParesisRelapsing herniationSensory disturbancesTransmission of disease of unknown etiology and transmission of infectious agents including but not limited to HIV, hepatitis, syphilis, or microbial contaminantsVertebral end plate inflammation

The following definitions should be used to assess intensity of AEs:Mild: Awareness of sign or symptom, but easily tolerated, i.e., does not interfere with participant’s usual function.Moderate: Discomfort enough to cause interference with usual activity.Severe: Incapacitating with inability to work or do usual activity, i.e., interferes significantly with participant’s usual function.

The investigator will assess causal relationship between an AE and the study product on the basis of his/her clinical judgment and the following definitions. The causality assessment will be made based on the available information and can be updated as new information becomes available.Not relatedPossibly relatedProbably relatedDefinitely relatedUnknown

AE disposition will be judged as follows:1 = recovered/resolvedThe participant fully recovered from the AE with no residual effect observed.2 = recovered/resolved with sequelaeThe residual effects of the AE are still present and observable.Include sequelae/residual effects.3 = not recovered/not resolvedThe adverse event itself is still present and observable.4 = recovering or resolving5 = fatal6 = unknown

Clinical actions required can include:1 = noneNo treatment was required.2 = medication requiredPrescription and/or over the counter medication was required to treat the AE.3 = hospitalization or prolongation of hospitalization requiredHospitalization was required or prolonged due to the AE, whether or not medication was required.4 = other

An SAE will be reported to the sponsor within 24 h of the study site becoming aware of the event and entered into the EDC system. The investigator will provide additional information on the SAE by updating the information on the CRFs and in the EDC as updates become available and transmitted to the sponsor. The sponsor may also ask for additional clinical reports including redacted source documents to be provided by the investigator to assist in the assessment of the event. Significant new information and updates will continue to be submitted promptly to the sponsor, entered on CRF pages, and in the EDC as they become available, and the investigator will follow the SAE until it is resolved, or no further improvement is expected.

The sponsor ensures that the investigator submits safety event notifications to the governing IRB within the timeframe specified by the IRB, when applicable. Acceptable means of confirming that the IRB requirements have been met include forwarding a copy of the written, signed report that was sent to the IRB to the sponsor. Copies of this report should be filed in the investigator’s site files and the sponsor’s clinical investigation files.

New SAEs will only be documented for each participant until the last study-related participant visit. In case of acute risk, the incident must be reported immediately.

### Frequency and plans for auditing trial conduct {23}

The investigator/investigational site will permit study-related monitoring, audits, IRB review, and regulatory inspections by providing direct access to source data/documents. Direct access includes permission to examine, analyze, verify, and reproduce any records and reports that are important to the evaluation of a clinical study. The investigator/designees will be responsible for obtaining and gathering information related to unexpected AEs and SAEs and reporting those as related to VIA Disc NP to their IRB, and to the product manufacturer.

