### Outcomes {12}

The primary efficacy endpoint is the proportion of participants who achieve a minimal clinically important difference (MCID), defined as at least a 30% reduction in back pain VAS score from baseline to 12 months, in the VIA Disc NP group compared to that in the sham control group [8, 9].

The primary safety endpoint will be the proportion of participants that experience one or more treatment-related (investigational product (IP) or procedure) adverse events (AE) in the VIA Disc NP group compared to the sham control group at 12 months.

Additional safety measures will include the following:Proportion of participants who experience an unexpected treatment-related serious adverse eventProportion of participants who experience any AEProportion of participants who experience each unique AE

Secondary efficacy endpoints include:Mean change in VAS score for back pain severity assessed at each follow-up intervalMean change in ODI score for back function assessed at each follow-up intervalProportion of participants who achieve at least a 50% reduction in VAS score for back pain severity (substantial clinical benefit (SCB)) assessed at each follow-up interval [10]Proportion of participants who achieve a patient acceptable symptom state (PASS), defined as a VAS score for pain severity of 30 mm or less, assessed at each follow-up interval [11, 12]Proportion of participants who achieve a MCID, defined as a 30% or greater improvement in ODI score assessed at each follow-up interval [8, 9]Proportion of participants who achieve SCB, defined as a 50% or greater improvement in ODI score assessed at each follow-up interval [13]Proportion of participants who achieve a PASS, defined as a ODI score for back function of 20 or less at all follow-up intervals [14, 15]Proportion of participants in each ODI functional impairment category assessed at each follow-up interval [16]Mean change in EQ-5D-5L score assessed at each follow-up intervalMean PGIC score assessed at each follow-up interval

For participants that have consented to opioid use assessment via prescription drug monitoring program (PDMP):Reductions in opioid use, defined as a ≥ 30% decrease in total dispensed morphine milligram equivalents (MME) from baseline to all follow-up intervals

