Monitoring visits will be documented on monitoring visit reports and will aim to verify that:Compliance with the clinical protocol and applicable regulations is being maintained.Source data are verified and signed off upon as accurate.Participant files are accurate and complete.Participant withdrawal has been documented (if applicable).Participant non-compliance has been documented (if applicable).The investigator and site staff are informed and knowledgeable of all relevant document updates concerning the clinical investigation.Only authorized individuals are performing study-related functions.The IP is being used according to the protocol and instructions for use.Staffing and facilities are adequate.Signed and dated ICFs have been obtained from each participant.CRFs and queries are complete.All AEs are reported to the sponsor.All SAEs and unanticipated adverse events (UAEs) are reported to the sponsor and the IRB.All other required IRB reports, notifications, applications, submissions, and correspondence are maintained in the investigator’s files and are accurate.Corrective and preventive actions have been implemented (if applicable).

To ensure that the study is conducted in accordance with the terms of the clinical protocol, study monitors must visit each study site at routine intervals throughout the duration of the study. The exact frequency of visits shall be determined on an individual study site basis as detailed in the clinical monitoring plan and shall depend upon the following factors:Rate of participant enrollmentExperience of the investigator in conducting clinical studiesRecord of previous site compliance

eCRFs will be completed in a 21 CFR Part 11-compliant EDC system for each participant consented into the clinical study. The study coordinator will enter the source data onto the CRF, and it will then be entered into the EDC and study monitors will verify that the source documents match the data entered on the CRF and in the EDC. Once verified, the study monitor will lock the field or page via a monitoring approval step so the data cannot be changed unless requested.

CRFs will be completed on paper forms for each participant consented for the clinical study. The study coordinator will enter the source data onto the CRFs, and data from the CRF pages will be entered into the EDC system. Study monitors will verify that the source documents match the CRFs at selected time intervals.

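### The protocol gives two different scopes for IRB reporting, and the narrower one, read literally, omits serious events attributed to the procedure rather than the product

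*Protocol article*

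**What the plan says.** Four places in the protocol article bear on what reaches the IRB.

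- **Section {18a}** (assessment and collection of outcomes) lists what monitoring visits verify. Two items are that "All AEs are reported to the sponsor" and that "All SAEs and unanticipated adverse events (UAEs) are reported to the sponsor and the IRB". Neither is limited by causality or by arm.
- **Section {22}** (adverse event reporting and harms) sends each SAE to the sponsor within 24 hours "of the study site becoming aware of the event and entered into the EDC system". For the IRB, it says the sponsor ensures that the investigator "submits safety event notifications to the governing IRB within the timeframe specified by the IRB, when applicable". On causality it says: "The investigator will assess causal relationship between an AE and the study product".
- **Section {23}** (auditing trial conduct) makes the investigator or designees responsible for collecting information on unexpected AEs and SAEs and for "reporting those as related to VIA Disc NP to their IRB, and to the product manufacturer".
- **Section {12}** (outcomes) bases the primary safety endpoint on participants with one or more events described as "treatment-related (investigational product (IP) or procedure) adverse events (AE").

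Section {21a} adds that the trial uses "two independent medical monitors to adjudicate all adverse events and deviations from protocol".

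**The concern.** An investigator reading section {23} and a monitor working from section {18a} hold different instructions about the same events. A site that reports to the IRB only what it judges related to the allograft follows the first and fails a check under the second. Sites that pick different sections would report unevenly.

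The difference falls on a particular kind of harm. Both arms undergo sedation and the insertion of a cannula, and only the active arm receives the product. A serious event caused by the needle pass or the sedation is not related to VIA Disc NP in the ordinary sense of those words. If section {23} governs, the IRB need not be told of it. The IRB has good reason to follow the risk of the sham procedure and of the delivery technique. Section {5d} states that there is no steering committee and section {21a} names two medical monitors, so the IRB is an important outside check.

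**Working it through.** No arithmetic applies. The check sets the sections side by side.

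**Step 1: are the event classes the same?** Section {18a} speaks of SAEs and unanticipated adverse events, abbreviated UAE. Section {22} defines an unexpected AE under the same abbreviation, and section {23} speaks of unexpected AEs and SAEs. I take these as the same two classes. What differs is the filter: none in {18a}, relatedness to VIA Disc NP in {23}.

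**Step 2: does section {22} settle the scope?** It leaves the timeframe to the IRB and qualifies the duty with the words on applicability in the quote above. It also asks for confirmation that IRB requirements are met. It does not list the events to be notified, so it does not clearly choose between the two scopes.

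**Step 3: apply each rule to four kinds of SAE.** Sedation is counted here as part of the procedure, and the attribution is taken as already made.

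| SAE attributed to | Sponsor within 24 h ({22}) | IRB under {18a} | IRB under {23}, read literally | Within the relatedness definition of the primary safety endpoint ({12}) |
|---|---|---|---|---|
| Cannula or sedation, sham arm | Yes | Yes | No | Yes |
| Cannula or sedation, active arm | Yes | Yes | No | Yes |
| Product, active arm | Yes | Yes | Yes | Yes |
| Neither product nor procedure, either arm | Yes | Yes | No | No |

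The two IRB columns disagree in three of the four rows. In the first two rows the trial's own safety endpoint counts the event while the literal reading of {23} does not send it to the IRB. Those rows cover both arms, so the dividing line is product versus procedure rather than active versus sham.

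**Step 4: is the causality rating able to carry a procedure attribution?** Section {22} rates causality against the study product and does not name the procedure. Section {12} needs attribution to product or procedure. The two should refer to the same thing, whichever IRB scope is chosen.

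**The case against.** The best defence has three parts.

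First, section {23} contains no word of exclusion. Its sentence is awkwardly worded and sits in the section on auditing, and a site that sends all SAEs and UAEs to the IRB satisfies both sections. Monitors check against {18a}, so under-reporting should be caught. This is fair, and it is why the finding is an inconsistency to reconcile rather than a settled failure to report. But section {23} is one of the places that state the investigator's own duty, and a site that follows it as written has not obviously departed from the protocol.

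Second, section {22} may hand scope as well as timing to the IRB. That reading is possible. It would then be a third rule, different from the unfiltered statement in {18a}, so it does not remove the need to reconcile.

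Third, the events are not lost. This stands in full: SAEs reach the sponsor within 24 hours, all AEs go to the sponsor, and the medical monitors adjudicate them. Section {23} also gives IRB review direct access to source data.

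A reader might go further and infer that the filter in {23} requires knowledge of the arm, or that a report sent under it discloses the allocation. The documents do not support either. Section {22} offers graded categories (possibly, probably, definitely related, unknown) that a blinded rater can use, and such a rating reveals nothing about the arm. Section {17a} already leaves the treating investigator unblinded, so the filter forces no new unblinding, and it does not list the IRB or the manufacturer among those blinded.

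A reader might also infer that no sham event could ever qualify and that the IRB would see one arm only. That holds only if the rater knows the arm, since a blinded rater could call a sham event possibly related to the product. Sections {22} and {23} do not say whether a blinded or an unblinded investigator makes the rating.

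**Conclusion.** The point holds as an inconsistency in the scope of IRB reporting. Sections {18a} and {23} state different rules, and {22} does not clearly say which applies. If {23} governs and is read literally, SAEs attributed to the procedure rather than the product fall outside IRB notification in both arms, which is narrower than the product-or-procedure definition in the primary safety endpoint. The causality reference in {22} has the same narrowness.

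The consequence is limited to IRB oversight. It would be wrong to conclude that serious harms of the sham procedure go unreported in the trial: they reach the sponsor and are adjudicated. The efficacy analysis is not affected. The number of events concerned cannot be given, because the article states no expected SAE rate in either arm.

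The conclusion rests on two assumptions: that unexpected and unanticipated events are the same class, as the shared abbreviation suggests, and that the full protocol, which is not shown, does not already resolve the scope. The correction should be made, since investigators and monitors now hold different safety-reporting instructions and the remedy is cheap.

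**What to change.** Reconcile sections {18a}, {22} and {23} into one statement of which events go to the IRB. It should apply equally to both arms and should not be filtered on relatedness to the product alone. Section {18a} already states such a scope and could serve as the common text. Use identical wording in the monitoring checklist and in the investigator's duties, and let {22} add the IRB's timeframe. Record causality as a field in the report instead of using it to decide whether a report is made.

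In section {22}, align the causality reference with the product-or-procedure definition in section {12}, so that the rating collected is the one the endpoint needs.

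The cost is protocol wording, with the IRB approval that section {25} requires for any amendment, a memo to sites, and at most a few more IRB notifications.

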### Plans for communicating important protocol amendments to relevant parties (e.g., trial participants, ethical committees) {25}

Any amendment to the study protocol that is deemed to be appropriate as the study progresses will be communicated to the investigator by the sponsor. All protocol amendments will undergo the same review and approval process as the original protocol. A protocol amendment may be implemented after it has been approved by the IRB. The sponsor will assure the timely submission of amendments to regulatory authorities.

### Dissemination plans {31a}

The clinical trial agreement between the sponsor and the study site and investigator shall govern the publication rights of the parties. The data provided by this clinical trial, and all related information and any materials containing such data and information, are the exclusive property of the sponsor and are confidential. The investigator or other study-related personnel may not disclose to anyone or use any data, information, or materials related to this clinical trial without the express prior written consent of the sponsor.

The sponsor may, in its sole discretion, publish the findings of the study in the peer-reviewed medical literature. Publication of the results will be based upon appropriate analyses and review of the complete data and will occur primarily under the direction of the sponsor, which will develop guidelines for authorship inclusion. Neither the investigator nor any other third party may publish the results of the study or any related information without the prior written consent of the sponsor in compliance with the executed clinical study agreement between such parties. The plan for publication of data is to be within 12 months of trial completion.

